### Hypothesis and objectives

1.2

Based on the published literature, we assume that allopathic and Ayurvedic treatments are equally effective in treating depression, both leading to improvements in symptom severity. Therefore, we do not expect any statistically significant difference in treatment effect between the treatment groups (between-group effect) in week 8. However, we hypothesize that both therapies will lead to an improvement in depression symptoms over a period of 8 weeks (within-group effect). The question is exploratory in nature due to the design and methodology.

This study will pursue the following scientific objectives:

Treatment Effect: To quantitatively compare the effect of allopathic and ayurvedic treatments (and their combination) in reducing the severity of depressive symptoms in MDD, as measured by validated rating scales (primary Montgomery-Åsberg Depression Rating Scale (MADRS), secondary Hamilton Depression Rating Scale (HAM-D) and Patient Health Questionnaire-9 (PHQ-9) at baseline, 8 weeks, 3 months and 6 months.Side Effects and Quality of Life: To compare the incidence, type, and severity of adverse events associated with allopathic and ayurvedic treatments using standardized adverse event reporting like Udvalg for Kliniske Undersøgelser Scale (UKU), General Assessment of Side (GASE) and Medication Adherence Report Scale (MARS). Furthermore, to assess differences in quality of life (QoL) and daily functioning between treatment groups using validated QoL instruments (e.g., WHOQOL-BREF) and functional assessment scales (e.g., Global Assessment of Functioning (e.g., Global Assessment of Functioning (GAF) and Functional Assessment Short Test (FAST).General Health Evaluation: To evaluate and compare changes in general health parameters (e.g., Body Mass Index (BMI), vital signs, relevant blood work indicators such as liver and kidney function tests, electrolytes, CRP, leukocytes, red blood cells, platelets, haemoglobin , haematocrit , red cell indices and TSH) across treatment groups over the study duration.

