### Sample size calculation and statistical analysis

2.9

We hypothesise that all treatment groups lead to a statistically significant reduction in symptoms of depression between baseline and week 8 (within group effect). We also hypothesize that the groups do not differ in terms of treatment success (between group effect). We performed a power analysis to calculate the sample size. With a sample size of N = 105 patients, an alpha error probability of 0.5 and a moderate effect size (0.5) (for change in symptoms of depression), we achieve a statistical power of >0.8. An effect size of 0.5 equates to a mean difference in the MADRS score between baseline and week 8 of 50%, which reflects a commonly accepted clinical response measure in depression studies. In practise , this would mean a reduction of 15 points on the MADRS scale from 30 points at baseline to 15 points at week 8. Such a kind of reduction has been seen in other interventional studies in depression.

Data analysis will be conducted by the team at the Department of Psychiatry, University of Münster. The primary and secondary outcome measures will be analysed using an intention-to-treat (ITT) and exploratory approach. We will focus on specialized analyzation for longitudinal data. In addition, we will correct for confounding variables in all analyses where significant differences arise between the groups.

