The choice of statistical test will depend on the nature of the data and the specific research question. For continuous outcome variables (e.g., scores on depression rating scales, quality of life scores, continuous physiological measures), Analysis of Variance (ANOVA) or independent samples t-tests will be used to compare means between the three treatment groups (Ayurvedic-only, Allopathic-only, and Combination). *Post-hoc* tests (e.g., Tukey’s HSD, Bonferroni correction) will be employed if significant differences are found between groups to determine which specific groups differ significantly. For categorical outcome variables (e.g., presence or absence of adverse events, categorical measures of quality of life, treatment adherence categories), Chi-square tests or Fisher’s exact tests (for small sample sizes) will be used to compare proportions between treatment groups. Given the repeated measures design (baseline, 8 weeks, 3 months, 6 months), appropriate statistical models for longitudinal data (e.g., repeated measures ANOVA, mixed-effects models) will be used to analyse changes in outcome measures over time within each treatment group and to examine the interaction effects between treatment group and time. This will allow for a more powerful examination of treatment effects and the assessment of treatment response trajectories. Strategies to address missing data will be carefully considered and documented. In addition to p-values, effect sizes (e.g., Cohen’s d) and 95% confidence intervals will be reported for all significant findings. All statistical analyses will be performed using appropriate statistical software packages (e.g., SPSS, R).

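### Effect sizes and confidence intervals are promised only for significant findings, so under the no-difference result it expects the plan does not commit to reporting the Ayurvedic-versus-allopathic difference with its interval

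*Protocol article*

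**What the plan says.** Two rules in the protocol article, both under Sample size calculation and statistical analysis (2.9), depend on significance:

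- Post-hoc procedures such as Tukey or Bonferroni "will be employed if significant differences are found between groups to determine which specific groups differ significantly".
- Beyond p-values, "effect sizes (e.g., Cohen’s d) and 95% confidence intervals will be reported for all significant findings".

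The expected result is stated under Hypothesis and objectives (1.2): "we do not expect any statistically significant difference in treatment effect between the treatment groups (between-group effect) in week 8". Section 2.9 repeats the no-difference hypothesis. Yet the first objective in section 1.2 is "To quantitatively compare the effect of allopathic and ayurvedic treatments (and their combination) in reducing the severity of depressive symptoms".

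Section 2.9 also names two analyses whose conduct does not depend on an earlier significant result. For continuous outcomes, "Analysis of Variance (ANOVA) or independent samples t-tests will be used to compare means between the three treatment groups". Longitudinal models (repeated measures ANOVA or mixed-effects models) with a group-by-time term are planned as well. No equivalence or non-inferiority margin is stated.

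**The concern.** The objective asks for a quantitative comparison of the arms. The reporting rule promises the quantities that would answer it, an effect size and an interval, only when a finding is significant. The authors predict that the between-group finding will not be significant. So the promise lapses in the very case they expect.

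What is at stake is how a null result will be read. The article assumes equal effectiveness and sets no margin, so the interval for the difference is the only output that separates arms that are close from arms measured too loosely to say. A bare non-significant p-value invites the reader to treat the hypothesis of no difference as confirmed. The article also wants its results to inform later randomised trials, and those need the estimate and its precision whether or not p falls below the threshold.

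**Working it through.** **Inputs.** From the article: 105 participants, about 35 in each of three groups; effect size 0.5; alpha printed as 0.5; power above 0.8. Assumed: alpha 0.05, equal SDs, all 35 per arm observed at week 8, and a MADRS SD of 8, 10 or 12 points, because the article gives none.

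**1. The plan's own figure.** The power statement concerns change from baseline to week 8. A paired t-test with n = 35, d = 0.5 and two-sided alpha 0.05 has noncentrality 0.5 × √35 = 2.96 and power 0.820, which agrees with a power above 0.8. It says nothing about the contrast between arms: a two-sample t-test with 35 per arm, d = 0.5 and alpha 0.05 has power 0.54.

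**2. How often the post-hoc step is not reached.** This takes the overall test to be a one-way ANOVA with 2 and 102 degrees of freedom. Its noncentrality is λ = N·f², where f is the root mean squared deviation of the three group means, in SD units.

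- *Arms equal:* the test is significant in 5% of trials by construction (simulation with 100,000 runs: 5.0%), so the step is not reached in about 95%.
- *Arms A and B 0.5 SD apart, C midway* (means 0, 0.25, 0.5): f = √[(0.25² + 0 + 0.25²)/3] = 0.204; λ = 105 × 0.0417 = 4.38; power 0.438. Not reached in 56%.
- *Arms A and B 0.5 SD apart, C equal to one of them* (means 0, 0.5, 0.5): f = √[((1/3)² + 2 × (1/6)²)/3] = 0.236; λ = 105 × 0.0556 = 5.83; power 0.558. Not reached in 44%.

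**3. What happens when the step is reached.** In the same simulation with C midway, a true A–B difference of 0.5 SD averages 0.70 SD among trials with a significant overall test, and a true 0.25 SD averages 0.57 SD. Estimates reported only after a significant result would be too large on average.

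**4. The interval that could be reported.** The unadjusted 95% half-width is t(0.975; 102) × SD × √(2/35) = 0.474 × SD:

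| Assumed SD | Half-width (MADRS points) | Share of the article's 15-point expected reduction |
|---|---|---|
| 8 | 3.8 | 3.8/15 = 25% |
| 10 | 4.7 | 4.7/15 = 32% |
| 12 | 5.7 | 5.7/15 = 38% |

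With Tukey adjustment the factor is 0.569, giving 4.5, 5.7 and 6.8 points.

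At SD 10, an observed difference of 0 gives an interval of −4.7 to +4.7, and an observed difference of 3 gives −1.7 to +7.7. Both are non-significant, but they mean different things. Only the interval shows this.

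**5. Sensitivity to alpha.** At the printed 0.5, the overall test would be significant in 50% of trials with equal arms and in about 89% to 94% of trials in the two 0.5 SD scenarios. The figures in step 2 therefore rest on reading alpha as 0.05.

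**The case against.** The strongest objection is that nothing here stops the difference from being estimated. A reader might infer from the post-hoc rule that the two treatments are compared only after a significant overall test, so that under the expected result their difference is never estimated and the between-group question cannot be answered. The article does not support that. The longitudinal model, which section 2.9 makes its focus, would yield group-by-time contrasts whatever the overall p-value. With three groups, independent-samples t-tests can only be pairwise, and no prior test is required for them. The sentence on intervals can also be read as a minimum: it does not say that non-significant contrasts will be withheld. All of this stands. It follows that the 95% and 44% to 56% figures count how often the post-hoc step is not reached, not how often an estimate is missing.

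A second objection is that the study calls itself exploratory and hypothesis-generating. This takes most of the force from a complaint about multiplicity: three uncorrected pairwise t-tests have a familywise error of about 12%, but that matters little where no confirmatory between-group claim is made. It does not excuse the reporting rule, since exploratory work depends on estimates and intervals more than on significance.

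A third is that an article leaves table contents and covariates to the full protocol or analysis plan. That is fair for such detail, and none is asked for here. The significance condition is different, because the article states it.

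What remains after all three is that the commitment to effect sizes and intervals covers significant findings only. A non-significant t-test or model contrast falls outside it too.

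**Conclusion.** The point holds as a fault in a stated reporting rule. In the result the authors expect, the plan does not commit to giving the Ayurvedic-versus-allopathic difference with its interval, and without that interval a non-significant p-value cannot be interpreted. It does not hold as a claim that the difference cannot or will not be estimated.

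Size: at an assumed alpha of 0.05 with 35 per arm and one-way ANOVA as the overall test, the post-hoc step is not reached in about 95% of trials with equal arms and in about 44% to 56% when A and B differ by 0.5 SD. The unadjusted pairwise interval would be about ±3.8 to ±5.7 MADRS points for assumed SDs of 8 to 12. Missing data would widen it, and adjustment for baseline could narrow it. The change should be made; the sample size is not affected. The printed alpha of 0.5 and the within-group basis of the power statement are separate matters.

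**What to change.** Three changes of wording in section 2.9:

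1. In the sentence on effect sizes and 95% confidence intervals, replace the restriction to significant findings with: *for all between-group comparisons, whether or not significant*.
2. Add that the three pairwise week-8 MADRS differences (Ayurvedic minus allopathic, combination minus allopathic, combination minus Ayurvedic) will be reported with 95% confidence intervals from the planned longitudinal model, whatever the overall p-value.
3. Add that a non-significant between-group result will not be read as equal effect, and that similarity will be judged from the width and position of the intervals.

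No new data, visits or participants are needed. The cost is slightly longer results tables.

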### Primary and secondary outcome measures

2.7

The primary endpoint will focus on changes in depressive symptom severity, measured using primary MADRS, and secondary HAM-D and PHQ-9 especially in week 8. The use of multiple scales enhances the reliability and validity of the assessment, providing a more comprehensive picture of symptom change. Several secondary outcome measures will exploratively elucidate the impact of treatments on various aspects of patient well-being and functioning. These include side effects (UKU, GASE, MARS), quality of life and daily functioning (WHOQoL-BREF, GAF, FAST) as well as general health measures (e.g. lab tests). This comprehensive approach ensures that the study captures a broad range of outcomes, providing a robust and nuanced evaluation of the treatment effect and side effects of allopathic and Ayurvedic treatments for MDD. The question is exploratory in nature due to the design and methodology.

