### Ethical considerations and data protection

2.8

Ethical considerations will guide all aspects of the study, from design and implementation to data analysis and dissemination. The research protocol was approved by the relevant Institutional Ethics Review Boards (IERBs) at participating institutions (MAM University approval number: MAM UNI/IECHR/2025; Bhaikaka University approval number: IEC/BU/162/Faculty/25/135/2025). In addition, the study was pre-registered with the Indian authorities (CTRI/2025/07/090147).

All potential participants will receive comprehensive information about the study’s purpose, procedures, risks, and benefits ensuring that participants can make an informed decision about their participation. Written informed consent will be obtained from all participants prior to any study procedures being undertaken. Participants will be free to withdraw their consent and discontinue their participation at any time without penalty. Participants will be closely monitored for the occurrence of adverse events throughout the study period. Regular follow-up visits will allow for the detection and assessment of any adverse effects, whether related to the study interventions or other factors. If any adverse events occur medical attention, adjustments to the treatment regimen, counselling, or other supportive measures as needed appropriate interventions will be provided promptly. Serious adverse events will be reported immediately to the relevant IERBs and the study team. The study will have a clear protocol for managing adverse events. A data safety monitoring board will regularly review safety data to ensure participant safety. The study’s data management procedures will strictly adhere to relevant data protection regulations, which includes GDPR Compliance, Indian Data Protection Standards, Local Data Safety Standards and Data Anonymization.

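### The only named comparison of adverse-event incidence is a test of crude proportions, which ignores how long each patient was observed and can mislead if retention differs between arms

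*Protocol article*

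**What the plan says.** Comparing side effects is a stated objective in section 1.2: "To compare the incidence, type, and severity of adverse events associated with allopathic and ayurvedic treatments". Section 2.7 lists side effects among the secondary outcomes.

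Detection depends on attendance. Section 2.8 says "Regular follow-up visits will allow for the detection and assessment of any adverse effects". Section 2.4 schedules visits every two weeks to week 8 and monthly after that to month 6, which makes eight post-baseline visits (weeks 2, 4, 6 and 8; months 3, 4, 5 and 6). Section 2.8 also allows withdrawal at any time.

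For the analysis, section 2.9 gives "presence or absence of adverse events" as an example of a categorical outcome, for which chi-square or Fisher's exact tests "will be used to compare proportions between treatment groups". It also says: "The primary and secondary outcome measures will be analysed using an intention-to-treat (ITT) and exploratory approach". On incomplete data it says only: "Strategies to address missing data will be carefully considered and documented".

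The article does not give the time window or denominator of the adverse-event proportion, the classification of patients who leave early, or an expected dropout rate.

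**The concern.** A test of two proportions has no term for length of observation. It compares like with like only if the arms were observed for similar periods. Nothing in the design secures that. Groups are formed by preference and clinical practice (section 2.1), the allopathic arm is at one hospital and the other two arms at another (section 2.3), and patients may be in- or outpatients (section 2.2.1).

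A patient who withdraws event-free after week 4 has attended 2 of 8 visits. If that patient stays in the denominator as a non-event, the proportion includes time in which nothing could be recorded. An arm that loses more such patients then shows a lower incidence at the same true risk. The article promises comparative evidence on side effects, so a difference in retention could be read as a difference in tolerability.

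**Working it through.** **Plan's own figure.** There is none to reproduce. The power statement in section 2.9 concerns change in depressive symptoms, and no adverse-event or dropout rate appears anywhere. All rates below are assumptions. Both models suppose equal true risk in every arm, loss unrelated to events, and leavers without an event counted as absent.

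**Model 1: loss spread over six months.** Let *R* be the true six-month risk and *D* the proportion lost by month 6, with constant hazards:

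- event hazard *l* = −ln(1 − *R*)/6; dropout hazard *m* = −ln(1 − *D*)/6
- crude proportion = *l*/(*l* + *m*) × [1 − exp(−6(*l* + *m*))] = *l*/(*l* + *m*) × [1 − (1 − *R*)(1 − *D*)]

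For *R* = 40% and *D* = 30%: *l* = 0.0851 and *m* = 0.0594 per month, so the crude proportion is 0.589 × (1 − 0.6 × 0.7) = 0.589 × 0.58 = 34.2%.

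| True risk | 10% lost | 30% lost | Gap, 10% v 30% (points) | 50% lost | Gap, 10% v 50% (points) |
|---|---|---|---|---|---|
| 20% | 19.0% | 16.9% | 2.1 | 14.6% | 4.4 |
| 40% | 38.1% | 34.2% | 4.0 | 29.7% | 8.4 |
| 60% | 57.4% | 51.8% | 5.6 | 45.5% | 11.9 |
| 80% | 77.0% | 70.4% | 6.6 | 62.9% | 14.1 |

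(Gaps are from unrounded values.) With 35 per arm and an assumed 5% level, an approximate power calculation for two proportions gives a falsely significant difference in about 4–9% of trials for 10% v 30%, and 7–25% for 10% v 50%. In the same model, events divided by observed person-months are unbiased: at *R* = 40% the rate is 0.0851 per month whatever the dropout.

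**Events only in the first 8 weeks.** With the event hazard confined to that period and dropout as before, 10% v 30% loss gives 19.7% v 19.0% (*R* = 20%), 39.4% v 38.1% (40%), 59.2% v 57.3% (60%) and 79.0% v 76.8% (80%). The gap is about 1 to 2 points.

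**Model 2: all loss at one visit.** Let *P* be the true risk over eight visits, with per-visit event-free probability *q* = (1 − *P*)^(1/8). A fraction *d* leaves after visit *k*:

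- crude proportion = (1 − *d*)*P* + *d*(1 − *q*^*k*)

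For *P* = 50% and *k* = 2 (week 4), 1 − *q*² = 0.159:

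- *d* = 30%: 0.7 × 0.5 + 0.3 × 0.159 = 39.8%
- *d* = 10%: 0.9 × 0.5 + 0.1 × 0.159 = 46.6%
- apparent risk ratio = 0.398/0.466 = 0.85 instead of 1.00

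For *k* = 4 (week 8), 1 − *q*⁴ = 0.293, giving 43.8% v 47.9% and a ratio of 0.91.

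**Reversal.** Take *R* = 60%. If one arm loses 30% of its patients, all after a recorded event, no event is missed and its crude proportion is 60%. If the other loses 10% unrelated to events, it shows 57.4% (table). Here the arm with more loss looks worse.

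**The case against.** Two stronger inferences are tempting, and the article supports neither.

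First, a reader might infer that the plan counts every early leaver as event-free for six months. It does not say so. Presence or absence appears only within a list of examples, intention-to-treat does not by itself settle how unobserved outcomes are filled in, and missing-data handling is left open. Presence could be a per-visit value: the side-effect scale GASE asks about the past week, and comparisons are planned at week 8, month 3 and month 6. A non-attender would then be missing. This objection stands as to what is stated. It does not rescue the method. Presence at one visit is not the incidence named in section 1.2, and restricting to completers would depart from intention-to-treat and drop those who left because of an event.

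Second, a reader might infer that the arm losing more patients must look safer. That holds when loss is unrelated to events, and the reversal example shows it is not general.

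It can also be said that denominators and windows are details an article leaves to the full plan, that longitudinal models are planned, and that the analysis is exploratory. The first is fair for the details, but the article does name a method, and that method ignores follow-up. On the second, section 2.9 says "appropriate statistical models for longitudinal data (e.g., repeated measures ANOVA, mixed-effects models) will be used" to analyse changes in outcome measures over time. It does not apply them to cumulative adverse-event incidence. Its adjustment for confounders addresses group differences, not observation time. The third limits the consequence: at 10% v 30% loss, false significance stays near the nominal level.

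**Conclusion.** The point holds in a limited form. The one method named for comparing adverse-event incidence ignores length of observation, in a non-randomised, two-hospital, six-month study with free withdrawal. If retention differs, and leavers without a recorded event count as absent, the comparison is distorted at equal true risk.

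Under assumed losses of 10% v 30% the size is modest in most scenarios: about 2 to 7 points with spread loss, 1 to 2 points with early events, and a risk ratio of 0.85 in the harsher case where all loss falls at week 4. It grows to 4 to 14 points at 10% v 50%. The true size and direction cannot be known from the article, which gives neither dropout nor event rates. The primary depression outcome is unaffected. This is an inexpensive improvement to the safety comparison.

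**What to change.** In section 2.9, make the between-arm comparison of adverse-event incidence account for observed time, in one of two ways:

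- event rates by Poisson or negative binomial regression, with the log of observed time or of attended visits as offset; or
- cumulative incidence of the first adverse event, censored at the last attended visit.

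Report at week 8 and month 6, with between-arm differences or ratios and 95% confidence intervals. Keep crude proportions as description, with visits attended per arm beside them, and state their denominator and time window.

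The offset should be chosen in advance: the first four visits span 8 weeks and the last four about four months, so visits and time are not interchangeable. A single six-month rate also assumes a constant rate. If events cluster early, cumulative incidence is the safer choice.

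The cost is analysis wording and some analysis work. The data must show the visit at which each event was first recorded and the last visit attended. The article names the data system but does not confirm that these items are held. The downside is the assumption that later risk in leavers resembles that in patients who stay, which is why the crude figures should remain alongside.

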**Methods:**

This six-month, naturalistic observational study will involve 105 adult participants (18–65 years) diagnosed with MDD according to DSM-5 criteria. Participants will be categorized to one of three groups: allopathic-only treatment (n=35), ayurvedic-only treatment (n=35), or a combination of both (n=35). Depressive symptom severity will be assessed as primary endpoint using primarily the MDRS, and secondarily HAMD and PHQ-9 scales at baseline, every 2 weeks until week 8, followed by monthly assessments until months 6. Secondary outcomes will exploratively include side effects (UKU, GASE, MARS), quality of life and daily functioning (WHOQoL-BREF, GAF, FAST) as well as general health measures (e.g. lab tests).

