### Trial design and study setting

2.1

This study employs a naturalistic observational (non-randomization) design, conducted within real-world clinical settings for a six-month period (see **Figure 1**) where the group assignment reflects patient preference and clinical practice in specialized hospitals. The study population comprises 105 adult participants. Participants will be observed in one of three treatment groups, each consisting of approximately 35 individuals, based on the treatment they receive (see **Figure 1**).

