### Study intervention

2.3

This study will utilize a naturalistic observational design, leveraging the established expertise and practices of two distinct clinical settings: Nadiad Ayurveda Hospital (for Ayurvedic only and combined treatments) and Shree Krishna Hospital, Department of Psychiatry, Bhaikaka University, Karamsad, Anand (for allopathic treatments). The assignment to the groups follows a clear system. The two hospitals have different areas of focus. One clinic (Shree Krishna Hospital) provides exclusively allopathic treatment, while the other (Nadiad Ayurveda Hospital) provides Ayurvedic treatment. Patients who are treated at the Ayurvedic hospital but have previously received allopathic treatment will continue to receive allopathic treatment (combined therapy). The clinic is selected based on clinical indications and in consultation with the patient.

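### The tests named for adverse-event incidence cannot carry the confounder correction that section 2.9 promises when the non-randomised arms differ

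*Protocol article*

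**What the plan says.** All references are to the protocol article.

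- **Objective (1.2).** One objective is "To compare the incidence, type, and severity of adverse events associated with allopathic and ayurvedic treatments". Side effects are secondary and exploratory (2.7).
- **Allocation (2.1, 2.3).** The study is not randomised: "the group assignment reflects patient preference and clinical practice in specialized hospitals". One hospital supplies the allopathic arm and the other supplies the Ayurvedic and combination arms. Section 2.3 describes the combination arm by treatment history: "Patients who are treated at the Ayurvedic hospital but have previously received allopathic treatment will continue to receive allopathic treatment (combined therapy".
- **Size (abstract).** The groups are "allopathic-only treatment (n=35), ayurvedic-only treatment (n=35), or a combination of both (n=35").
- **Test for binary outcomes (2.9).** "For categorical outcome variables (e.g., presence or absence of adverse events, categorical measures of quality of life, treatment adherence categories"), the plan is: "Chi-square tests or Fisher’s exact tests (for small sample sizes) will be used to compare proportions between treatment groups".
- **Confounding (2.9).** "we will correct for confounding variables in all analyses where significant differences arise between the groups".
- **Longitudinal models (2.9).** Repeated measures ANOVA and mixed-effects models are given as examples for changes in outcome measures over time. No version for a binary outcome is named.
- **Limitations (3.2).** Potential confounding and selection bias are acknowledged.

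**The concern.** Two statements in section 2.9 do not fit together. One fixes the test for adverse-event incidence. The other promises a correction that this test cannot carry out. A plain chi-square or Fisher test compares crude proportions and has no place for age, baseline severity or any other patient characteristic.

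The condition attached to the promise, that the groups differ significantly, may well be met, because hospital, preference and treatment history decide who enters which arm. An arm that takes in patients more prone to adverse events, whatever the treatment, will show a higher crude incidence even if the treatments are equally safe. The opposite imbalance could hide a real difference. The comparison of side effects is a stated objective, so the choice of test affects something the study means to report.

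**Working it through.** **The plan's own figure.** The article gives no adverse-event rate and no power for adverse events. Its only power statement (above 0.8, for N = 105 and effect size 0.5) concerns change in depressive symptoms. It reproduces for a within-group paired t-test with n = 35 at two-sided 0.05 (0.82). It has no bearing on this point.

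**Step 1: can the named test deliver the promised correction?**

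| Statement in 2.9 | What it requires | Met by a plain chi-square or Fisher test? |
|---|---|---|
| Proportions compared by chi-square or Fisher | A table of arm by event | Yes |
| Confounders corrected in all analyses where groups differ significantly | A covariate or stratifying term | No |

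The mismatch follows from the text alone and needs no assumed numbers.

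**Step 2: what if the named test is used alone?** Assumptions, none taken from the article apart from the group size: 35 vs 35; no treatment effect; one baseline risk factor x, standard normal in the reference arm and shifted by m SD in the other; two-sided 0.05.

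logit P(event) = log(0.40/0.60) + log(2) · x

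Averaged over x, the event risk is about 41% in the reference arm. In the other arm it is about 49% at m = 0.5 and 53% at m = 0.8. The spurious risk differences are therefore 49 − 41 = 8 and 53 − 41 = 12 percentage points. Rejection rates over 6,000 simulated trials per setting:

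| Imbalance m (SD) | Chi-square | Fisher | Logistic with x |
|---|---|---|---|
| 0 | 4.9% | 2.9% | 5.2% |
| 0.3 | 5.6% | 3.5% | 4.3% |
| 0.5 | 8.9% | 5.5% | 4.6% |
| 0.8 | 16.3% | 11.1% | 4.9% |

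Independent repeats gave about 9% for chi-square at 0.5 SD and about 15–16% at 0.8 SD.

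**Step 3: three arms of 35.** Assumptions: no treatment effect; a binary risk factor; event risk 20% without it and 40–60% with it; 2,000 trials per setting.

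| Prevalence of the factor by arm | Chi-square | Adjusted logistic |
|---|---|---|
| 50/50/50% | 4–5% | 5–6% |
| 40/40/60% | 7–10% | 5–6% |
| 30/30/70% | 11–28% | 5–6% |
| 20/20/90% | 25–72% | 5–6% |

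**Step 4: what if the conditional promise is carried out?** The rule simulated is: adjust by logistic regression when the factor differs between arms at p < 0.05, otherwise use chi-square. Rejection is about 4–5% in the two-arm setting at 0.3–0.8 SD, and 5–7% in all imbalanced three-arm settings. Error is largely controlled under this rule.

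**Step 5: how often does the condition trigger?** For a two-sample t-test with 35 per arm at two-sided 0.05, power is about 0.54 for a true 0.5 SD difference (about 55% in simulation) and roughly 0.9 for 0.8 SD. In the three-arm setting, a 40/40/60% imbalance was detected in about 39–40% of trials. Rejection stays low even so because the trials that miss the trigger are those in which the observed imbalance happens to be small.

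**The case against.** **The plan already promises correction.** The sentence covers all analyses, adverse events included, and can be read as an addition to the listed tests. Step 4 shows that, carried out with a regression model, it works well. This stands as an answer to the size of the problem, but not to the mismatch: the adjusted binary method it depends on is nowhere named, and the method that is named cannot do the job.

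**A journal article leaves model detail to the full plan.** That is fair, and the lack of a covariate list or model formula is not the complaint. The complaint is that the article makes an affirmative choice of test which conflicts with its own sentence on confounding.

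**The longitudinal models might cover side effects.** The article does not exclude this, since side-effect scales are listed among the outcome measures. But presence or absence of adverse events is explicitly assigned to the tests of proportions.

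**It is not peculiar to adverse events.** This is true: the plain ANOVA and t-tests for continuous outcomes carry no covariates either. For those, however, the same section also names mixed-effects models, which can.

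**The outcome is secondary and exploratory, and confounding is admitted.** Both are true and both limit the weight of the point. Admitting confounding as a limitation does not provide a method for it.

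A reader might infer that the study will report case-mix differences as differences in harm, or that correction is promised unconditionally. The article supports neither: the promise is conditional on significant group differences, and nothing says it will be dropped for adverse events.

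**Conclusion.** The point holds as a mismatch within section 2.9: the test fixed for adverse-event incidence cannot carry the correction promised for it, and no adjusted method for binary outcomes is named.

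The size depends on what is done in practice. With the named test alone, and under the assumptions of Step 2, a true null is rejected about 9% of the time at 0.5 SD imbalance and about 15–16% at 0.8 SD (Fisher about 5.5% and 11%), with spurious risk differences of about 8 and 12 points. With the conditional correction made by regression, rejection is about 4–7%. Event rates, the strength of the risk factor and the imbalance are all assumed, because the article gives none of them, and the illustrations assume that the confounder is measured and enters the model.

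The weakness that remains under the conditional rule is the significance trigger, which at 35 per arm misses a 0.5 SD imbalance nearly half the time. This is worth correcting, since the change is cheap, but it does not threaten the primary endpoint.

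**What to change.** In section 2.9, make a covariate-adjusted binary regression the main comparison of adverse-event incidence across the three arms: logistic, or modified Poisson with robust errors, with Firth-penalised logistic regression when events are few. Use one or two baseline covariates that are already collected, for example baseline symptom severity and age, fixed in advance and not chosen by significance testing. Report adjusted risk differences with 95% confidence intervals. Keep chi-square or Fisher as the comparison labelled unadjusted.

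The cost is a few sentences and one standard model, with no new data and no change to care. Intervals may be somewhat wider, and rare events will support few covariates. The model will not separate treatment from hospital, or the combination arm from the treatment history that section 2.3 uses to describe it. Those stay as limitations.
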